## Introduction

Type 1 diabetes mellitus (T1DM) is a chronic disorder caused by autoimmune damage to the insulin-producing pancreatic beta cells, leading to elevated blood glucose concentration (hyperglycaemia).^1^ T1DM requires exogenous insulin treatment,^2^ of which hypoglycaemia is a potential side effect.^3^ The prevalence of T1DM globally is 5.9 per 10 000 with the incidence of 15 per 100 000 people.^4 5^ In the UK, the prevalence is reported as fifth highest with 8.6%, and incidence of T1DM is rising 5% every year.^5^ There is no cure for diabetes; therefore, effective management can be pivotal in reducing risk of adverse events as well as delay the onset of long-term complications.^6 7^

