#### Secondary objective

To examine the impact of physical activity and diet on glycaemic events and incorporate relevant features into the model.

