### Study protocol

#### Calorimetry room

The participant will stay in the calorimetry room for up to 36 hours, during which there will be set times for meals, light exercise and rest. Meals will be provided with known total energy and macronutrient content. Water will be provided ad libitum. While in the calorimetry room, wearable sensors will record physiological data continuously.

Other activities will be performed during this time, specifically: (a) up to 12 serial blood samples of 30 mL will be obtained from a peripheral venous catheter inserted at the beginning of phase 1 to measure venous glucose and insulin concentration, (b) finger-prick blood samples will be taken periodically for capillary glucose measurements, (c) up to 12 saliva samples will be taken to analyse salivary concentration of cortisol and melatonin, (d) all urine will be collected as voided for protein oxidation analysis, (e) movement and activity will be assessed by motion sensors, (f) simple questionnaires will be used to measure food intake and activity as well as subjective aspects such as appetite, satiety and wellness, and (g) daytime blood pressure will be monitored using an ambulatory blood pressure monitor (hourly readings).

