#### Free-living

While free-living, the participant will continue to wear the monitoring devices to record ECG and glucose concentration. If tolerated, participants will also be fitted with an ambulatory blood pressure monitor for the first 24 hours of the free-living phase. Instructions will be provided on how to affix and operate the devices. During this time, participants will also be required to keep brief diaries detailing physical activity, food intake and sleep. The first is a daily activity diary, to be completed at the end of each day, detailing: any device removal and replacement, physical activity, food intake, alcohol intake and caffeine intake. The second is a standardised sleep diary, the Consensus Sleep Diary-M,^28^ to be completed on waking in the morning.

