#### Covariates

The autonomic nervous system is responsible for maintaining homeostasis and regulates processes such as blood pressure,^36^ digestion,^37^ metabolism^38^ and circadian rhythm,^39^ all of which may affect cardiac function and show as changes in the ECG morphology.^40–43^ Additionally, exercise can affect the QT interval, that is the ECG section representing ventricular depolarisation, due to exercise-induced autonomic response.^44^ During phase 1 of the study, daytime blood pressure will be monitored, and the calorific value and macronutrient composition of meals will be recorded. Additionally, exercise sessions will be scheduled throughout the phase. Throughout the free-living phase, all meals, exercise duration and intensity, and sleep times will be recorded by the participant. The data collected via this protocol enable us to examine how the covariates relate to the outcome of interest, that is, the glycaemic status, by performing statistical tests such as analysis of variance.^45^ The recording of mealtimes, exercise and sleep enables the data to be analysed during distinct periods of interest such as post-exercise or postprandial.

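### The free-living records omit insulin dose and timing and do not flag food taken to treat a low, so phase 2 diet and activity associations cannot be separated from insulin

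*Protocol article*

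**What the plan says.** The secondary objective reads: "To examine the impact of physical activity and diet on glycaemic events and incorporate relevant features into the model". The data for it in phase 2 come from diaries and sensors. The Free-living section describes a daily activity diary, "to be completed at the end of each day", that covers "any device removal and replacement, physical activity, food intake, alcohol intake and caffeine intake". A standardised sleep diary is completed on waking.

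The Covariates section describes the free-living record a second time: "all meals, exercise duration and intensity, and sleep times will be recorded by the participant". It says the data collected allow the relation between covariates and glycaemic status to be examined, "by performing statistical tests such as analysis of variance".

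On insulin, the Introduction states that "T1DM requires exogenous insulin treatment", "of which hypoglycaemia is a potential side effect". The only insulin measurement in the article is in phase 1, where up to 12 venous samples are drawn "to measure venous glucose and insulin concentration". Insulin dose is not listed in either phase.

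**The concern.** Every participant takes a treatment that the protocol itself links to the outcome, and the free-living record as described does not capture it. If people with type 1 diabetes dose for meals and change the dose around exercise, insulin is tied to both exposures of the secondary objective as well as to the outcome. A test of diet or activity against glycaemic status then shows the combined result of the behaviour and the insulin that went with it, with no data to separate the two.

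Food eaten to correct a low raises a different problem. It is recorded, because it falls under food intake, but nothing distinguishes it from an ordinary meal. Here the low causes the eating. An analysis that treats all eating as an exposure can find that food goes with hypoglycaemia.

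The Data modelling section and the Discussion plan to put activity, mealtimes, meal composition and sleep into the detection model. A feature that partly records the response to a low would carry the outcome into the predictors and flatter the model's performance.

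**Working it through.** **Inputs.** Phase 1 lasts up to 36 h and phase 2 up to 3 days (Study setting). Full participation gives 108 h (Sample size). Participants may enrol in either or both phases (Enrolment procedure). Up to 12 venous samples are taken in phase 1 (Calorimetry room). Glucose is reported every 15 minutes (Continuous glucose monitoring).

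**The plan's own figure.** 36 + 3 × 24 = 36 + 72 = 108 h, which matches.

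**Share of recording with no insulin information.**
- Both phases in full: 72 / 108 = 67%.
- Phase 2 only: 72 / 72 = 100%.
- Phase 1, for comparison: 36 h / 12 samples is about one insulin concentration every 3 h, if evenly spaced (assumption).

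These are shares of recording time, not sizes of bias.

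**What is recorded in free-living.**

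| Item | Free-living section | Covariates section |
|---|---|---|
| Food or meals | yes | yes |
| Exercise or activity | yes | yes, with duration and intensity |
| Sleep | yes (separate diary) | yes |
| Alcohol, caffeine, device removal | yes | not named |
| Insulin dose or timing | not named | not named |
| Flag for food taken for a low | not named | not named |

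**What the missing insulin does to a diet coefficient.** This is an illustrative linear model for glucose level; the article gives none. Suppose

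glucose change = a × C − b × I + error,

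where C is carbohydrate, I is insulin, and a and b are positive. Write I = k × C + u, where u is dosing unrelated to the carbohydrate eaten. The coefficient on C without insulin in the model is then

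a − b × k.

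- k < a/b: positive, but smaller than a.
- k = a/b: zero.
- k > a/b: negative.

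The sign depends on k, which the plan does not record. If u = 0, insulin and carbohydrate are perfectly collinear, and recording insulin would not separate a from b. Separation needs variation in u. Basal, correction and exercise-related dosing would supply it, which is assumed here as ordinary self-management and is not stated in the article.

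**Food taken for a low.** The order of events is low, then eating. The diary is completed once a day, so the time of eating rests on recall, whereas glucose arrives every 15 minutes. Without a flag made at the time, it may not be possible to tell afterwards whether an entry preceded a low or answered it.

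**The case against.** The strongest case against has four parts.

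1. **The article is a summary.** The two lists of free-living data differ, so neither need be exhaustive, and the actual diary form is not shown. This is fair: the article does not prove that insulin goes unrecorded. But it itemises the diary down to caffeine and device removal, restates the covariates, and says the data suffice to examine them, with insulin absent each time. That goes beyond ordinary condensation.

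2. **Meal-related insulin is partly an intermediate.** A dose taken because of a meal lies on the path from the meal to glucose. The net quantity a − b × k is then a legitimate effect of eating under usual care, and a zero or negative value is not an error in itself. This stands. The protocol does not say that it wants the effect with insulin held fixed. The remaining point is that the net effect is the only one obtainable, and that dosing not driven by the meal stays uncontrolled.

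3. **The use is largely predictive.** The Discussion describes lifestyle habits as predictors, and a predictor needs association only. This answers much of the insulin point for the model, but not the objective's wording about impact. It does not answer the problem of food taken for a low, because a predictor that follows from the outcome is a fault in a prediction model too.

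4. **The scope is limited.** Phase 1 has scheduled meals and exercise, known meal content and sampled insulin. This stands.

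A reader might infer more: that food eaten for a low is not recorded, that insulin is the main cause of hypoglycaemia here, or that the whole secondary objective fails. The documents support none of these. Such food is recorded but unmarked. The Introduction calls hypoglycaemia a potential side effect and points to several contributing factors. The gap is in the free-living part.

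**Conclusion.** The point holds for phase 2. As described, the free-living record contains neither insulin dose and timing nor a marker for food taken to treat a low. Diet and activity associations with glycaemic events there are net of unrecorded insulin and cannot be separated from it. Unmarked treatment food adds reverse causation, which is a distinct fault and can leak the outcome into the lifestyle features.

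The gap reaches up to 67% of a full participant's recording and all of a phase-2-only participant's. The direction and size of any bias are unknown.

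The conclusion rests on two assumptions that the article does not state: that dosing is commonly adjusted around meals and exercise, and that some dosing varies independently of carbohydrate, so that recording it would help. Detection from the ECG alone does not depend on this. The change is worth making because it is cheap and the information is difficult to recover after data collection.

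**What to change.** - **Diary.** Add the time, type and amount of each insulin dose as taken in usual care (or a pump download), and a tick-box with time for food taken because glucose was low.
- **Analysis.** Report diet and activity associations twice: without insulin, as the net effect under usual care, and with insulin included. State which question each answers.
- **Model features.** Exclude flagged food from exposures and predictors, and treat it as a consequence of the episode.
- **Participants already completed.** Where these items are missing, label the free-living diet and activity results as descriptive associations.

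The cost is a minor diary amendment and a little more work for participants. Sessions began in December 2022, so early participants will lack the items and the insulin-adjusted analysis will cover only part of the sample. No change to anyone's treatment is implied.

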### Devices

#### Continuous glucose monitoring

Continuous glucose levels will be measured using a FreeStyle Libre 2 flash glucose monitoring system, which can be worn for up to 14 days. Although the sensor is sampling continuously, the glucose concentration is reported in 15-minute intervals. The sensor can store data for a period of 8 hours. As such, data will be extracted at regular intervals using a smartphone preconfigured with the companion application. The sensor is water resistant and can be used while bathing, showering, swimming or exercising, and is worn on the back of the upper arm. The device has been evaluated for accuracy and user experience and found to have been generally well received by patients with T1DM who used it for 10–14 days.^29^

#### ECG

Medtronic Zephyr BioPatch is a CE-marked device, indicating that the product complies with European Union safety, health and environmental requirements, which operates across one lead within an ECG amplitude range between 0.25 and 15 mV, with a sampling frequency of 250 Hz. The device will be affixed to the wearer’s skin via two electrodes placed in the centre of the chest. It can also be worn in a secondary configuration attached to a fabric harness, which is worn across the chest if the electrodes are not tolerated. The Zephyr BioPatch also has additional sensors to record physiological parameters such as activity levels, posture and breathing rate, which are all reported at 1 Hz.^30^ The device will be removed before bathing, showering or swimming, and reaffixed afterwards. The battery is rated for 35 hours of continual use. Each participant will be provided with fully charged devices for the free-living phase of the study.

### Data management

All data collected are owned by the UHCW National Health Service (NHS) Trust. All electronic data, physiological or otherwise, generated as part of this study will be anonymised and stored in the HMRU database on secure servers and backed up and protected in accordance with NHS guidelines. Anonymised data will be made available to researchers for analysis under an Institutional Data Sharing Agreement between the UHCW and University of Warwick. Data will be extracted from the devices, anonymised, stored and made available for analysis when the participant has concluded the protocol.

### Data analysis and modelling

#### Data processing

The effect of glycaemic events on the ECG signals will be examined. It is anticipated that ECG signals will be affected by noise and artefacts due to body movement or heavy respiration. Therefore, we will apply preprocessing methods such as baseline wander removal to the raw signal to remove low-frequency noise. We will then identify individual heartbeats in the ECG and detect fiducial points using our ECG segmentation tool,^31^ which has been used in a recent study for cardiovascular disease detection.^32^ Heartbeats will then be grouped into 15-minute excerpts, corresponding to the sampling of the CGM, and annotated with the glycaemic state (ie, hypoglycaemic, normal, hyperglycaemic) according to the thresholds defined in table 1. Due to the lower sample frequency of the CGM, we will perform linear interpolation to estimate glucose measurements at every second.

**Table 1 T1:** Glycaemic event thresholds for people with T1DM^51–57^

Glycaemic event	Blood glucose concentration (mmol/L)
Severe hypoglycaemia	<2.8
Hypoglycaemia	>2.8 and <3.9
Euglycaemia	>3.9 and <11.1
Hyperglycaemia	>11.1 and <13.9
Severe hyperglycaemia	>13.9

T1DM, type 1 diabetes mellitus.

#### Data analysis

Data will be obtained from several days of continuous physiological monitoring of participants. During analysis, the data will be divided into smaller excerpts such as 1, 2 or 5 min intervals. In addition, beat-level ECG samples will be analysed; therefore, the total number of samples available during analysis is ambiguous.

Characteristics of an ECG can be represented by heart rate variability (HRV) parameters and can be categorised into time-domain features, frequency-domain features and non-linear features.^33^ We aim to use physiological signal processing packages such as NeuroKit2^34^ and HeartPy^35^ to determine these features. Furthermore, we aim to determine ECG beat parameters, which include length and slope among the fiducial points (P, Q, R, S and T). We will perform statistical tests to determine the statistical significance of different HRV features and ECG morphology parameters among different glycaemic values to determine which parameters are associated with hypoglycaemia.

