The self-monitoring of blood glucose (SMBG) can play a key role in effective management of diabetes. SMBG can empower patients to adhere to lifestyle interventions, such as changes to diet and exercise regimen, as they have access to immediate feedback on the effects.^8^ Active participation from the patient in their care has been shown to improve outcomes such as reducing the risk of diabetic complications.^9^ Current methods for glucose monitoring have several limitations. The most common method for SMBG is an invasive ‘finger-prick test’ in which a small sample of blood is collected from the fingertip and analysed by a handheld device called a glucometer. This invasive procedure has several documented barriers preventing SMBG such as inconvenience, cost and discomfort.^10^ Moreover, the devices and associated consumables are prone to error if not operated correctly,^11^ requiring repeat attempts and generating unnecessary waste. Hypoglycaemia typically occurs during sleep,^12^ and those receiving insulin therapy are at increased risk due to a combination of factors such as impaired counter-regulatory hormone response and warning symptoms going unobserved.^13^ This presents an obvious limitation to the effectiveness of an invasive ‘finger-prick test’ as a tool for SMBG. An alternative to ‘finger-pricking’ are continuous glucose monitoring (CGM) devices, which require a small cannula inserted in the top layer of skin to continuously measure glucose in the fluid between the cells. They can be described as minimally invasive as after the initial fitting, they are routinely worn continuously for up to 14 days. However, despite being shown to be a beneficial tool for SMBG, national clinical guidelines for the UK do not recommend routine use of CGM devices for the management of T1DM due to insufficient evidence demonstrating their efficacy and cost-effectiveness.^14^

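### The tests that link HRV and ECG features to hypoglycaemia name no adjustment for sleep, time of day or posture, and the covariate analysis as worded would not remove that confounding

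*Protocol article*

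**What the plan says.** Five places in the protocol article bear on this.

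- **Data analysis.** The feature-level step reads: "We will perform statistical tests to determine the statistical significance of different HRV features and ECG morphology parameters among different glycaemic values". Its purpose is "to determine which parameters are associated with hypoglycaemia". No test, model, covariate or stratum is named.
- **Covariates.** Blood pressure, digestion, metabolism and circadian rhythm are listed as autonomic processes, "all of which may affect cardiac function and show as changes in the ECG morphology". Exercise is added because of its effect on the QT interval. The stated use of the covariate data is to "examine how the covariates relate to the outcome of interest, that is, the glycaemic status, by performing statistical tests such as analysis of variance". The section closes: "The recording of mealtimes, exercise and sleep enables the data to be analysed during distinct periods of interest such as post-exercise or postprandial".
- **Devices, ECG.** The patch has "additional sensors to record physiological parameters such as activity levels, posture and breathing rate, which are all reported at 1 Hz". Posture and breathing rate are not named in any analysis section. Data processing mentions heavy respiration, but only as a source of noise.
- **Introduction.** "Hypoglycaemia typically occurs during sleep".
- **Data modelling.** Activity levels and sleep patterns, from sensors and diaries, are to be included in the detection models.

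**The concern.** The Primary objective includes determining how ECG-derived features relate to glycaemic status, and the tests under Data analysis answer that part. A feature can differ between low and other excerpts because glucose is low, or because low excerpts come more often from people who are asleep, lying down or at a particular point of the circadian cycle. The article supplies both halves of this problem: it says lows cluster in sleep, and it says circadian rhythm and exercise alter the ECG.

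The stated covariate analysis does not separate the two explanations. Testing whether sleep or exercise relates to glycaemic status shows that a confounder exists. Removing its effect requires holding it fixed in the comparison of the feature across glycaemic states. At stake is the list of parameters reported as associated with hypoglycaemia, which could contain markers of night or posture.

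**Working it through.** The plan states no figure on this point. The 30 participants are a pragmatic target with no alpha, power or effect size, so there is nothing to reproduce. The mechanism can be sized only under assumptions.

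**From the document:** 30 participants; 36 h + 3 × 24 h = 108 h of data each with full participation.

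**Assumed:** no true effect of glucose on the feature; within-person SD of 1; lying shifts the feature by *d* = 0.3, 0.5 or 1.0 SD; people lie down in 33%, 50% or 67% of low excerpts and 33% of the others; two-sided 5% test. A low means an excerpt in the hypoglycaemic range.

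**Step 1, bias.** Spurious difference = *d* × (lying share in lows − lying share otherwise).
- 50% v 33%: 0.3 × 0.17 = 0.05; 0.5 × 0.17 = 0.09; 1.0 × 0.17 = 0.17 SD.
- 67% v 33%: 0.3 × 0.34 = 0.10; 0.5 × 0.34 = 0.17; 1.0 × 0.34 = 0.34 SD.

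**Step 2, false-positive rate.** Two simulations, each analysed correctly with the participant as unit (per-person difference, then a t-test across persons):
- A: 8 low and 300 other independent excerpts per person, 3,000 runs.
- B: 108 h per person in 5-minute windows, autocorrelated noise (time constant 30 min), on average 4 lows of 45 min, lying from 23:00 to 07:00 (8/24 = one third of the time), 300 runs.

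| Lying share, low v other | *d* (SD) | Rate, A | Rate, B |
|---|---|---|---|
| 33% v 33% | 0.3 / 0.5 / 1.0 | 6% / 5% / 5% | not run |
| 50% v 33% | 0.3 | 12% | 10% |
| 50% v 33% | 0.5 | 24% | 18% |
| 50% v 33% | 1.0 | 63% | 47% |
| 67% v 33% | 0.3 | 31% | 23% |
| 67% v 33% | 0.5 | 70% | 48% |
| 67% v 33% | 1.0 | 99.5% | 92% |

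**Hand check of one cell (A, 67% v 33%, *d* = 0.5).** Variance of one person's difference = 1/8 + 1/300 + 0.25 × 0.67 × 0.33/8 + 0.25 × 0.33 × 0.67/300 = 0.1250 + 0.0033 + 0.0069 + 0.0002 = 0.1354. Standard error over 30 people = √(0.1354/30) = 0.067. The bias is 0.17/0.067 ≈ 2.5 standard errors against a critical t of 2.05, which gives a rejection rate of roughly 69%, in line with the simulated 70%.

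**Step 3, number of people with lows.** In the same cell of A, the rate is 70% with 30 participants, 51% with 20 and 27% with 10. The bias itself stays at about 0.17 SD; more data only makes it more likely to be declared significant.

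**Step 4, conditioning on posture.** Comparing within the same posture gives 4.4-5.1% in A. Putting lying in the per-person regression gives 4-6% in B.

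**The case against.** The strongest reply is that the article condenses a fuller plan. Data analysis does not say that the tests are unadjusted, and an adjustment set is commonly left to an analysis plan, which is not shown here. Covariates says that meal, exercise and sleep records allow analysis by period; a comparison of low and non-low excerpts within sleep would remove much of a night-time effect. Data modelling brings in activity and sleep, and motion sensors are used in the calorimetry room.

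Much of this stands, and it limits the point:

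- A reader might infer that the plan excludes posture, activity and breathing, or never lets covariates near the feature comparison. The text does not say so. It names no adjustment and leaves period-based analysis open.
- A reader might infer that features with no true link to glucose would then be carried into the detection models. Nothing says these tests select model inputs, and the models already include activity and sleep.
- The simulations do not show that patch posture is better than the sleep records. In B, lying is simply the night period, so stratifying by night would work as well. In A, the posture effect cancels by construction once posture is held fixed.
- The rates follow from chosen inputs. Sample size says the number of hypoglycaemic episodes cannot be anticipated, and participants may join only one phase.

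What the reply does not meet is that the article does state how covariates will be used, and that use does not protect the feature comparison. Period-based analysis is a possibility not tied to the HRV and ECG tests, and its examples are post-exercise and postprandial, not sleep. Including sleep and activity in the detection models is a separate step and adjusts none of these tests.

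**Conclusion.** The point holds as an inexpensive improvement to the association analysis. The covariate plan, as worded, relates covariates to glycaemic status and leaves the feature comparison open to confounding by sleep, time of day and posture, although the article itself says that hypoglycaemia clusters in sleep.

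The size cannot be taken from the documents. Under the assumed lying shares and shifts, a feature with no true link to glucose is declared associated in about 10% to over 90% of studies, with a spurious difference of about 0.05 to 0.34 SD. If lying shares are equal across glycaemic states, the rate stays near 5%. No single figure in that range should be read as a prediction. The conclusion rests on lows being unevenly spread over sleep and posture, which the Introduction implies, and on those states shifting the features. The article accepts the latter for circadian rhythm and exercise; for posture it is an assumption.

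**What to change.** Under Data analysis, state that each feature's association result comes from a within-participant model of the feature on low/not low, adjusted for sleep/wake or time of day and for patch posture. Equivalently, compare low and non-low excerpts matched within person on these. Clock time is the safest of the adjusters, because glucose cannot change it.

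Report the unadjusted contrast beside the adjusted one. Add activity and breathing rate as a further, separately labelled step. Hypoglycaemia may itself change them (the Abstract lists trembling and confusion among its symptoms), so adjusting for them may remove part of a true effect. Under Covariates, say that the covariates enter the feature comparison as well as being related to glycaemic status.

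The cost is wording, code and some extra analysis; the signals and sleep times are already collected. There is a small loss of precision, and with matching, participants without comparable low and non-low excerpts contribute nothing, so their number should be reported.
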